### Study sequence

Figures 1 and 2 represent the study sequence and timelines for procedures, respectively. Additional file 4 contains the Standard Protocol Items: Recommendations for Interventional Trials (SPIRIT) Checklist.

**Fig. 1 Fig1:**
[figure not shown]
Flow chart of study. BMI body mass index, BP blood pressure, HbA1c glycated haemoglobin, HN001 *Lactobacillus rhamnosus* HN001

**Fig. 2 Fig2:**
[figure not shown]
Study timeline and procedures. ^a^ Washout period of 1 month if subject has used probiotic supplements, systemic antibiotics, or short-term systemic steroids prior to enrolment. ^b^ Discussions/contacts to maintain adherence and study participation. ^c^ Shortened version of the Depression Anxiety Stress Scale (DASS 21) and Short-form health survey version 2 for New Zealand/Australia (SF-36). ^d^ Stanford Leisure-Time activity categorical Item (L-Cat 2.2). ^e^ Weight, height (and body mass index), blood pressure. ^f^ Glycated haemoglobin (HbA1c), fasting glucose, insulin, and lipids and additional bloods bio-banked for mechanistic studies. ^g^ Faecal samples to enable examination of possible mechanistic effects of study interventions

### Recruitment

Multiple recruitment strategies will be used to recruit participants to the study. Working with local primary health organizations, individuals with pre-diabetes will be invited by letter to join the study. In addition, the general public will be notified about the study through study posters, study information sessions, relevant email lists, and other hardcopy and online media.

All those expressing an interest in the study will be assessed for eligibility by a screening questionnaire and measurement of HbA1c.

### Information and consent

Potential participants will be provided with trial information through study videos available on a study website, written information and consent forms, and detailed discussions with field staff prior to screening and study enrolment. Information and consent forms will cover participation in the F4H study, and a separate information and consent form for the collection of additional biological samples (faecal samples and blood) to be bio-banked for later analysis.

Field research staff will obtain formal written informed consent at the commencement of the enrolment visit. Participants will attend four morning study visits in a fasted state. See Fig. 2 for the study timeline.

### Data and sample collection

Study data will be collected and managed using Research Electronic Data Capture (REDCap) tools hosted at the University of Otago, Dunedin, New Zealand. REDCap is a secure, web-based application designed to support data capture for research studies, providing: 1) an intuitive interface for validated data entry; 2) audit trails for tracking data manipulation and export procedures; 3) automated export procedures for seamless data downloads to common statistical packages; and 4) procedures for importing data from external sources. Field staff will complete the majority of data input; however, participants will self-complete the more sensitive questions online. These include the DASS 21, SF36, income, smoking, alcohol, drug use, mental health history, physical exercise, and bowel symptom questions. In addition, the 9-month data collection will not require a face-to-face visit with the field staff. Apart from those who are unable to complete questionnaires electronically and require a telephone interview, participants will complete all 9-month questionnaires online.

Field staff will use inbuilt REDcap data queries to check the completeness of all data and inbuilt range checks will be used to prevent data entry errors. Any changes to data will be recorded in the REDcap data log, and records of any data, which is checked or amended, will be completed using the REDcap database’s data query system.

#### Staff training

To ensure that high-quality and consistent data are collected, all field staff will be trained in the administration of study questionnaires and assessments of physical measures according to standard study protocols.

Field staff will instruct the participant on the completion of the SF36 using standard recommended procedures [42]. Anthropometric and blood pressure data will be collected using clearly defined protocols, standardized and calibrated equipment, and with duplicate readings and range checks to ensure data reliability. See Additional file 2 for equipment and protocols for anthropometric and blood pressure measures.

Staff trained in phlebotomy procedures will collect fasting blood according to a standardized protocol. After centrifuging, aliquots of serum or plasma will be stored at −80 °C until processed. Analysis will be performed in batches containing all of an individual’s samples to minimize measurement error due to batch variability. Those consenting to the collection of faecal samples will collect these samples in the 2–3 days prior to each study visit immediately after completing the 3-day food diary. See Additional file 5 for details on the blood and faecal sample collection and quality-control protocols.

#### Protocol deviations

Any participants who temporarily or permanently cease taking study interventions will be encouraged to remain in the study and data will be collected as per protocol. If such participants are unwilling to complete all further assessments, the first priority will be collection of primary outcome data (HbA1c at 6 months and related questions), followed by all other 6-month data. If participants withdraw completely, data collected to the time of their withdrawal will be included in the intention-to-treat analysis, and reasons for withdrawal will be reported.

#### Access to data

Only fieldworkers will have direct access to the study database. Participants will be allocated a unique study code, and data will be de-identified prior to export from the database or analysis. Data will be stored securely for at least 10 years and a possible indefinite period following this in accordance with the consent procedures for this study.

### Data monitoring

Due to the low-risk nature of the project, internal safety and data monitoring will occur by the named investigators. There will be no interim analysis of results and trial-stopping guidelines are considered unnecessary.

To monitor the study, reports of any participants ceasing the interventions and reasons for this will be presented at monthly meetings, and further investigations made if any concerns are identified. If for any reason unbinding to study capsule allocation is required, this will be done by a non-fieldworker contacting the randomization code holder at Fonterra Co-Operative Ltd.

Analysis of HbA1c, lipids, and mental well-being outcomes will occur after all participants have completed the 6-month intervention to inform the qualitative study and economic analysis (see below).

### Qualitative study

The accompanying qualitative study aims to explore whether participants in the β-glucan-based cereal arms find interventions acceptable or not in order to enhance the robustness of the study findings and inform translation to real-life settings [55–58]. The qualitative study will include: 1) approximately 24 qualitative semistructured interviews with participants from the two β-glucan cereal arms of the randomized controlled study, and the same participants will join one of four focus groups; and 2) three focus groups each with about eight to ten health professionals to discuss how they might translate the findings into long-term use in real-life clinical settings. It is intended that the qualitative data be collected in tandem with quantitative methods and purposefully integrated into study findings [59, 60].

#### Participants

A purposive sample of around 24 participants, six each from Māori*,* Pacific, South Indian and other ethnic groups enrolled in the β-glucan cereal arms, will be invited to join the qualitative study. We will use diversity sampling to include a gender, age, education, and socioeconomic mix. Participants will be asked to take part in an individual interview at 2 months and join one of four focus groups at around 6 months following completion of the intervention.

A purposive sample of health professionals will be invited to join the study as part of three focus groups. Diversity sampling will include a range of health promoters, community health workers, dieticians, health navigators, general practitioners, nurses, and pharmacists.

#### Data collection

A combination of individual interviews and focus groups will be used. Individual interviews allow one-to-one engagement, whereas focus groups prompt for additional information/revelations through social interaction not likely elicited individually [61]. The face-to-face audio-recorded individual interviews will follow a semistructured interview schedule. Questions will include how the interventions have been used, factors which may influence adherence, social and cultural beliefs about food, health, probiotics, pre-diabetes, diabetes, food, and health literacy, as well as potential for behaviour change and self-management. The focus group interview schedule will be informed by the data from the individual interviews and will further explore the acceptability of the interventions, real-world experience, differences between Māori, Pacific, South Indian and other ethnicities, and forecast how the interventions could be used in the long term. Focus groups with health professionals will explore their views on the acceptability of the intervention, barriers or facilitators to implementation, and draw on their experiences working with people with pre-diabetes or diabetes in general.

#### Analysis

The interviews will be transcribed verbatim. Transcripts will be imported into Nvivo 11 and a researcher (JH) will code in two ways: first, according to the content framework of questions [62, 63]; and second, according to meaning units and themes [64, 65]. The coding will then be shared with the research team (EM, BG, and SP), and consensus will be obtained through discussion and the testing of examples to ensure reliability.

### Economic analysis

The aim of the economic analysis is to model the potential cost-effectiveness of the intervention if it were implemented in a wider New Zealand context. The change in HbA1c, BMI, blood pressure, and serum total cholesterol observed at 6-month follow-up in the randomized controlled trial will be used in the model as estimates of the effectiveness of the intervention. These changes in risk factors will be modelled through to a change in incidence of the relevant diseases and then onto changes in quality-adjusted life years (QALYs), costs or cost savings to the health system (in 2011 New Zealand dollars; NZ$) and incremental cost-effectiveness ratios which show the health system cost per QALY gained. A health system perspective will be used, and benefits and costs will be modelled using a lifetime horizon. Outputs will be discounted at 3%.

The intervention will be modelled using a multi-state life-table (MSLT) model populated with rich New Zealand health data. An existing MSLT model, which is parameterised for the whole of the New Zealand population [66, 67], will be re-parameterised to the New Zealand population with pre-diabetes using data from routinely collected administrative health data (Healthtracker and the Integrated Data Infrastructure) and the Adult Nutrition Survey 2008/2009. In order to estimate the difference in QALYs and health system costs between the model’s intervention and business-as-usual (BAU) comparator, the entire New Zealand population alive in 2011 will be simulated out until death.

The BAU model uses projected all-cause mortality and morbidity rates by sex, age, and ethnicity (Māori and non-Māori). The model includes 14 diseases related to the included risk factors where proportions of the population simultaneously reside: coronary heart disease (CHD), stroke, T2DM, osteoarthritis, and multiple cancers (i.e. endometrial, kidney, liver, oesophageal, pancreatic, thyroid, colorectal, breast, ovarian, and gallbladder). The proportion of the New Zealand population in each disease life-table is a function of the disease incidence, case fatality, and remission (the latter in cancers only). Morbidity will be quantified (separately by sex, age, and ethnic group) for each disease using the years of life lived with disability (YLDs) from the New Zealand Burden of Disease Study divided by the population count to give prevalent YLDs. Disability weights from the Global Burden of Disease Study 2010 will be used to estimate the health status valuation of these YLDs [68].

Relative risks for the association between the relevant risk factors (HbA1c, BMI, blood pressure, and serum total cholesterol) and disease incidence will be sourced from the Global Burden of Disease study [69] or recent meta-analyses. These relative risks will be combined with the changes in risk factors through population impact fractions [70] to give the proportionate change in future disease incidence. The model will also capture the change in CHD and stroke incidence from the changing incidence of diabetes.

Time lags from the change in intervention-related risk factors to change in disease incidence is allowed for by using the average risk factor change over a previous window of time of 0 to 5 years for CVD, diabetes, and osteoarthritis, and 10 to 30 years for cancers. Probabilistic uncertainty about the boundaries (5, 10, and 30 years) will also be specified.

The proportionate change in disease incidence changes the ‘inflow’ to each of the multiple parallel disease sheets in the model. Each 5-year age cohort alive in 2011 is modelled out until their death in one ‘overall’ master life-table. The cohort is rewarded with health (i.e. QALYs) and health system costs in each annual cycle. This ‘overall’ master life-table has annual mortality, morbidity and costs that are mathematically linked to the multiple parallel disease life-tables. As the inflow (i.e. disease incidence) to a parallel disease life-table reduces (e.g. falling diabetes incidence), this reduces the morbidity, mortality, and costs of disease.

Health system costs (sex- and age-specific) will be calculated in 2011 NZ$ using individually linked data for publicly funded (and some privately funded) health events occurring in 2006–2010, including hospitalizations, inpatient procedures, outpatients, pharmaceuticals, laboratories, and expected primary care usage. Building on an existing framework [71] for calculating the timing of health system costs, the whole cohort will be assigned a sex- and age-specific annual health system cost of a citizen without an intervention-related disease and not in the last 6 months of their life. Additional disease-specific excess costs will be assigned to people: 1) in the first year of an intervention-related disease diagnosis; 2) in the last 6 months of life if dying of the given disease; and 3) otherwise prevalent cases of each disease. Costs will be modelled over the lifetime of the cohort, including costs both related and unrelated to the modelled diseases (meaning increased longevity due to the intervention will contribute to increased health system costs for some cohort members). How the intervention will be scaled up to the national level will be conceptualised, including estimating the cost of the intervention (see Cleghorn et al. [66] for an example of our methods). These estimates will be used in the model as estimates of the proportion of the total pre-diabetic population in New Zealand that will receive the intervention.

The excel model will be run 2000+ times using Monte Carlo simulation through an Ersatz add-in which samples from the uncertainty interval around each input parameter. This allows the calculation of QALYs and costs with the appropriate amount of uncertainty. Results from this programme of research will be disseminated widely. See Additional file 6.

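### As described, the economic model adds an end-of-life cost only for deaths from a modelled disease, so the terminal-cost part of any savings from lower modelled-disease mortality is overstated

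*Protocol article*

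**What the plan says.** All of this is in the Economic analysis section of the protocol article.

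- **Base cost.** The article states that "the whole cohort will be assigned a sex- and age-specific annual health system cost". That cost is defined as the "cost of a citizen without an intervention-related disease and not in the last 6 months of their life", so end-of-life spending is excluded from it by definition.
- **Additions.** "Additional disease-specific excess costs will be assigned to people" in three numbered situations: the first year after diagnosis of a modelled disease, "in the last 6 months of life if dying of the given disease", and otherwise as a prevalent case.
- **Scope of disease.** "The model includes 14 diseases related to the included risk factors".
- **Mortality and follow-up.** "The BAU model uses projected all-cause mortality and morbidity rates", and "the entire New Zealand population alive in 2011 will be simulated out until death". The horizon is lifetime and outputs are discounted at 3%.
- **Unrelated costs.** The section says that costs not related to the modelled diseases are also counted, "meaning increased longevity due to the intervention will contribute to increased health system costs for some cohort members".

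**The concern.** The base cost leaves out the last 6 months of life, and the list of additions puts it back only for people who die of a modelled disease. No item covers the last 6 months of someone who dies of anything else.

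In a model that follows everyone to death, preventing a death from a modelled disease moves that death to a later date, and often to another cause. The first terminal cost is removed from the intervention run. If the later death is from a non-modelled cause, nothing explicit replaces it. The saving credited is then nearly a full terminal cost, when the real saving is mostly the gain from paying it later.

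Cost-effectiveness is one of the three overarching aims, and the Discussion says the economic analysis is meant to inform funders. A structural omission of this kind is not covered by the Monte Carlo runs, because those vary the inputs that are present and cannot represent a cost that is absent.

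**Working it through.** The article states no cost, saving or ratio on this point, so there is no figure to reproduce. The check has a structural part and an illustrative part.

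**1. What each kind of death is charged, as described**

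| Person in the last 6 months of life | Base cost | Addition listed |
|---|---|---|
| Dying of a modelled disease | yes, non-terminal level | disease-specific terminal excess |
| Has a modelled disease, dying of another cause | yes, non-terminal level | prevalent-case excess, which may or may not contain some end-of-life spending |
| Has none of the 14 diseases, dying of another cause | yes, non-terminal level | none |

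**2. Why the gap does not cancel between runs.** Mortality is all-cause and everyone is followed to death, so in each run

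modelled-disease deaths + other-cause deaths = cohort size.

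Any net fall in modelled-disease deaths is therefore matched by an equal rise in other-cause deaths. The uncharged deaths are more numerous in the intervention run, and their timing differs.

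**3. Size per postponed death.** From the article: discount rate 3%. Assumed: a terminal cost of 1 unit whatever the cause; postponement by D years; a share p of postponed deaths finally due to a non-modelled cause and not charged.

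- True saving = 1 - 1.03^-D
- Saving as described = 1 - (1 - p) x 1.03^-D

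For D = 10, 1.03^-10 = 0.744:

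| p | As described | True | Ratio |
|---|---|---|---|
| 0.3 | 1 - 0.7 x 0.744 = 0.479 | 0.256 | 1.9 |
| 0.5 | 1 - 0.5 x 0.744 = 0.628 | 0.256 | 2.5 |
| 0.7 | 1 - 0.3 x 0.744 = 0.777 | 0.256 | 3.0 |

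Over the same range of p, the ratio is 2.9 to 5.4 at D = 5 and 1.5 to 2.3 at D = 15.

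**4. Sensitivity to equal terminal costs.** If a non-modelled death costs only half as much at the end of life, the true saving is 1 - (1 - p + 0.5p) x 1.03^-D. At D = 10 this gives:

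- p = 0.3: 1 - 0.85 x 0.744 = 0.368 true, 0.479 as described, ratio 1.3
- p = 0.7: 1 - 0.65 x 0.744 = 0.516 true, 0.777 as described, ratio 1.5

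**5. Cross-check with a two-cause life table.** Assumed: start at age 60; annual hazard 0.00003 x exp(0.095 x age); modelled diseases 20%, 35% or 50% of that hazard; modelled-disease mortality cut by 5% or 20%; 3% discounting.

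- Averted modelled deaths reappear one for one as other-cause deaths. At a 35% share and a 5% cut, the changes are -0.0116 and +0.0116 per person.
- In that case the discounted terminal saving as described is 0.0070, and the uncharged other-cause terminal cost is 0.0048, which is 68% of it.
- Across all the settings, charging other-cause deaths removes 62-73% of the discounted terminal saving if terminal costs are equal, and 31-36% if other-cause terminal cost is half as large.

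**The case against.** **The costing rests on a cited framework that is not shown.** The section says it builds on existing work for the timing of costs, and an article condenses. That framework may hold a terminal cost for other causes. This stands as a reason to allow for a mere error of description. It does not remove the point: the text is not silent, but defines a base cost and numbers the additions, and followed as written these produce the gap.

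**The prevalent-case item may absorb part of it.** Someone with a modelled disease who dies of another cause is still a prevalent case, and that average may include end-of-life spending, depending on how it is estimated. The Background puts eventual type 2 diabetes, one of the 14 diseases, at up to 70% of people with pre-diabetes. This stands. The clean omission concerns people with none of the 14 diseases, and the uncharged share may be below the assumed 30-70%.

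**A reader might infer that the section contradicts its aim of counting unrelated costs.** It does so only in part. The section explains that aim through added longevity, and the base cost does charge unrelated annual costs in every added life-year. Only the terminal phase is missing.

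**A reader might also infer that the error always favours the intervention.** It does not. Effects come from the observed changes in four risk factors and are sampled with their uncertainty. If a change or a draw is adverse, modelled-disease deaths rise and the sign reverses. A postponed death that still occurs from a modelled disease is charged correctly.

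**Conclusion.** The point holds for the cost rules as described. Deaths from non-modelled causes carry no explicit terminal cost, and where the intervention lowers modelled-disease mortality the terminal-cost part of the savings is overstated.

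With equal terminal costs and a 10-year postponement, the model credits 0.48 to 0.78 of a terminal cost against a true 0.26. The overstatement is smaller if other-cause deaths are cheaper at the end, if postponement is longer, or if the prevalent-case item already holds part of the cost. Only the 3% discount rate comes from the article; the other inputs are assumptions.

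These ratios apply to the terminal-cost component alone. First-year and prevalent-case costs, the cost of the intervention and the QALYs are not affected by them. It would be tempting to conclude that a net cost could be turned into an apparent saving. The document gives no terminal costs, no share of deaths from modelled causes and no effect size, so the effect on total cost or on the cost-effectiveness ratio cannot be computed and that conclusion has no support.

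The trial's HbA1c outcome and its analysis are untouched. The matter is worth correcting because it is directional whenever the intervention reduces modelled-disease mortality, and it is easy to correct.

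**What to change.** 1. Add a cost for the last 6 months of life when dying of any non-modelled cause, by sex and age, estimated from the 2006-2010 linked data already in use. Apply it in both the business-as-usual and the intervention run.
2. Define the prevalent-case phase to exclude the last 6 months of life, so that terminal spending is not counted twice.
3. If the cited framework already includes such a cost, correct the description in the Economic analysis section instead.

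The price is one more cost input, with its own uncertainty distribution, and possibly a less favourable cost-effectiveness ratio. No new data collection is needed.

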### Analysis plan

All primary analyses will be based on intention-to-treat principles with all individuals analysed in the group to which they were randomized. Demographic and baseline characteristics will be summarised using descriptive statistics. The primary outcome is HbA1c at 6 months. The primary analysis for the main outcome variable will be analysis of covariance (ANCOVA) with the baseline measurement of HbA1c as a continuous covariate, and the randomized treatments as main effects, and their interaction as categorical explanatory variables. Adjusted analyses will be conducted to include potential baseline confounding variables (BMI, level of exercise and total daily energy intake), and whether medications that could affect glucose metabolism were used after randomization. The effect of change in weight, change in exercise, and change in total daily energy intake between baseline and 6 months on HbA1c will also be explored using ANCOVA. A linear mixed model using all of the three HbA1c measurements and an appropriate random effects structure to account for correlation between repeated measurements, and using HbA1c at baseline as a continuous covariate, will be used as a sensitivity analysis for the effect of the randomized treatments. Subgroup analysis will use interaction terms (with treatment) for whether treatment effects vary by ethnicity, sex, or socioeconomic status.

Secondary outcome variables will be analysed in a similar way, with the most important outcomes for each being the 6-month time point. All outcome variables will be analysed with their baseline value as a continuous covariate. Subsequent sensitivity analyses will be guided by the outcome of this, with the introduction of relevant baseline covariates for each outcome variable. Factors which may affect mental health and well-being outcomes such as alcohol, recreational drug use, and life stressors will be described and considered in the analysis. Additional file 3 contains tables for baseline characteristics and results.

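### The economic simulation is described as sampling each input from its own interval, but four effect inputs come from the same participants; drawn without their covariance, they would misstate the uncertainty around QALYs.

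*Protocol article*

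**What the plan says.** All quotations are from the Economic analysis section of the protocol article.

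- **Source of the effect inputs.** Effectiveness is taken from the trial's own results: "The change in HbA1c, BMI, blood pressure, and serum total cholesterol observed at 6-month follow-up in the randomized controlled trial will be used". All four inputs come from one trial at one visit.
- **How they combine.** "These relative risks will be combined with the changes in risk factors through population impact fractions", giving a proportionate change in disease incidence. Changes in diabetes incidence also feed through to coronary heart disease and stroke.
- **How uncertainty is propagated.** The spreadsheet is to be simulated at least 2000 times by Monte Carlo, and for this the software "samples from the uncertainty interval around each input parameter".
- **What this is said to achieve.** "This allows the calculation of QALYs and costs with the appropriate amount of uncertainty".
- **Other uncertain inputs.** For the time lags, "Probabilistic uncertainty about the boundaries (5, 10, and 30 years) will also be specified". Relative risks and costs are inputs too.

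The section does not say that draws are independent. It also does not mention a covariance matrix, a joint distribution or resampling of participants.

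**The concern.** An interval around a single parameter describes that parameter's marginal distribution only. Four effects estimated in the same people, by four regressions on the same randomized groups, have correlated sampling errors whenever the outcomes are correlated within person after adjustment for baseline. A chance imbalance between arms in one outcome then tends to come with an imbalance in the others.

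The Analysis plan section suggests that some of these outcomes are related. It lists BMI as a potential confounder for HbA1c and will explore "The effect of change in weight, change in exercise, and change in total daily energy intake between baseline and 6 months on HbA1c".

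If each effect is drawn from its own interval with no link to the others, chance errors that move together in reality are allowed to cancel across a simulation run (or, with negative correlation, errors that offset each other are not). The spread of simulated QALYs is then not the spread implied by the trial. The Discussion says the economic results are meant to inform funders, and the trial behind the four effects is small: 152 recruited, or 114 with the planned 25% drop-out (152 × 0.75).

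**Working it through.** The article states no standard error, interval or correlation for the effects, the QALYs or the costs, so it has no figure of its own to reproduce. The correlations and weights below are **assumptions**, shown as a range.

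**Step 1: variance of a combined effect.** Approximate the health gain as a sum of four terms. Let w be each term's contribution on the SD scale (the model's sensitivity to that effect times its standard error). Let r be a common correlation between the four estimates.

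- Variance with the covariance kept: Σw² + r[(Σw)² − Σw²]
- Variance under independent draws: Σw²
- Ratio of the correct SD to the independent SD: √(1 + rK), where K = [(Σw)² − Σw²] / Σw²

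**Step 2: K for four patterns of contribution.**

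- Equal: (16 − 4)/4 = 3
- Variance shares of 50/25/15/10% (w is the square root of each share, Σw = 1.9106): 3.6505 − 1 = 2.65
- HbA1c 70% on the SD scale, the others 10% each: (1 − 0.52)/0.52 = 0.923
- HbA1c 90% on the SD scale, the others 3.33% each: (1 − 0.8133)/0.8133 = 0.230

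**Step 3: SD ratio (above 1 means independent draws give too narrow an interval).**

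| r | Equal | 50/25/15/10% of variance | HbA1c 70% | HbA1c 90% |
|---|---|---|---|---|
| −0.2 | 0.63 | 0.69 | 0.90 | 0.98 |
| −0.1 | 0.84 | 0.86 | 0.95 | 0.99 |
| 0.1 | 1.14 | 1.12 | 1.05 | 1.01 |
| 0.2 | 1.26 | 1.24 | 1.09 | 1.02 |
| 0.3 | 1.38 | 1.34 | 1.13 | 1.03 |
| 0.4 | 1.48 | 1.44 | 1.17 | 1.04 |

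For example, with equal contributions and r = 0.4, √(1 + 0.4 × 3) = √2.2 = 1.48. Ratios of 1.14 and 1.48 correspond to an interval 12% and 33% too narrow (1 − 1/1.14 and 1 − 1/1.48, from unrounded ratios).

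**Step 4: dilution by other inputs.** If the four effects make up a share s of the output variance under independent draws, the ratio for the whole output is √(s × ratio² + 1 − s). With s = 0.5 and r from 0.1 to 0.4:

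- Equal contributions: √1.15 = 1.07 to √1.6 = 1.26
- HbA1c 70%: 1.02 to 1.09

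**Step 5: check without the additive approximation.** A simulation of 200,000 draws used a multiplicative risk model with four equal effects. The 95% interval width was 0.318 at r = 0, 0.404 at r = 0.2 and 0.443 at r = 0.3. The ratios are 0.404/0.318 = 1.27 and 0.443/0.318 = 1.39, against 1.26 and 1.38 from the formula.

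**What was not computed.** These figures concern the health effect only. Cost per QALY is a ratio, and its spread also depends on how costs and QALYs move together, which the article does not give.

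**The case against.** The strongest reply is that independence is an inference. To say that every input is sampled within its interval is to say that every input carries uncertainty. Correlated draws also fall within each parameter's interval. The article gives the Monte Carlo a single sentence, builds on an existing published model, and refers to a fuller protocol available on request. A condensed article may reasonably leave the correlation structure to such sources, so its silence is not in itself an error.

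The reply also bears on direction and size. No correlation is given, the plan only intends to explore whether weight change relates to HbA1c, and nothing comparable is said about blood pressure or cholesterol. If HbA1c or the non-trial inputs dominate, the effect is slight.

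Most of this stands, and it limits the point. A reader might infer that the draws are certainly independent, that the interval is bound to be too narrow, or that the cost-per-QALY interval and any probability of cost-effectiveness would be overconfident. The documents support none of these. The first is not stated. The second needs positive correlation between effects acting in the same direction. For the third, nothing on costs was or could be calculated, and a probability of cost-effectiveness is not an output the article names.

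What remains is more than silence. The article describes one sampling method, in terms of each parameter's own interval, and says that this method yields the right uncertainty. Followed literally, the method carries no covariance and cannot guarantee that. The section's one pointer to an example of earlier methods is attached to scale-up and intervention cost, not to the sampling.

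**Conclusion.** The point holds conditionally and is minor. If the four trial effects are drawn parameter by parameter without their covariance, the uncertainty around QALYs is misstated: too narrow with positive correlation, which is plausible, and too wide with negative correlation.

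For the part of the uncertainty due to the trial effects, and assumed correlations of 0.1 to 0.4, the SD would be understated by a factor of about 1.14 to 1.48 with equal contributions and about 1.0 to 1.2 if HbA1c dominates. For the whole output it is less, in proportion to the variance carried by relative risks, lags and other non-trial inputs. With correlations of −0.1 to −0.2 the SD would instead be overstated (ratios 0.84 to 0.63 with equal contributions). These figures rest on assumed correlations and weights, none of them from the article. The direction for cost per QALY is open, and the primary HbA1c analysis is unaffected.

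**What to change.** State in the Economic analysis section that the four 6-month effects are drawn jointly, and do so by one of two routes:

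1. **Bootstrap.** Resample participants within each of the four randomized cells, refit the four 6-month ANCOVAs in each resample, and keep the four estimates together as one row. Each of the 2000+ model runs reads one row.
2. **Multivariate normal.** Estimate the covariance of the four effects from the trial and draw all four from that distribution in each run.

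Either route preserves whatever correlation the trial shows, positive or negative, so its sign need not be assumed in advance. The other inputs can be sampled as now.

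The cost is slightly more analysis work, mainly a table of draws read into the existing spreadsheet model, and possibly a wider reported interval. No new data are needed. If the draws are already joint, one sentence saying so settles the point.
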